### **8.3 Data management**

Data will be gathered anonymously by means of an eCRF which uses a remote single-entry system with electronic check of data congruence. Together with the usual data entry functions and on-line checks, this system, employing mobile devices (tablet, smartphone), created at the Research and Innovation Unit of Parma, also includes a control check of operator identification (investigator), check of patient eligibility criteria and of data entry required by the three questionnaires used in the study. To reduce missing data, a banner will appear warning the patient to complete all fields or to indicate unwillingness to answer, when some fields are left empty. If > 50% of responses is missing, the research nurse will indicate the reasons in the eCRF (see paragraph 8.9).

### **8.5 Blinding**

Blinding will be ensured both for patients, who will not be aware of the study epoch (control period or post-intervention period) in which they are providing information on their HRQoL, and for the statistician, who will use anonymized data and crypted identification codes for the study epochs. This should prevent ascertainment, performance, and attrition biases [Spirit guideline, [www.equator-network.org](http://www.equator-network.org)]. The nature of the intervention precludes blinding for clinical staff.

### **8.6 Sample Size**

The number of subjects to be enrolled was defined following the methodology for incomplete, cross-sectional Stepped-wedge cluster randomized trials [Hussey 2007, Hemming 2013, Hemming 2014; Hemming 2016] considering:

- a) 3 clusters, each comprising 5 centers and with equal size for each cluster (capacity of enrolment per week);
- b) an expected mean difference deemed clinically acceptable lying between 3 and 8 points of at least one domain (social or emotional), values indicated in the paper by Cocks et al [Cocks 2011], as minimal clinically relevant differences for the domains of this study;

- c) an ICC (Intra-class correlation coefficient) equal to 0.80, as reported in two papers [Uwer 2011, Lundy 2014 ];
- d) the Wald Test, with time as fixed effect and cluster as the random effect [Hussey 2007]
- e) a power of 80% and two-tail alpha of 5%;
- f) drop-out of 20% at follow-up [Ledderer 2013].

Applying the *steppedwedge* di STATA/MP 11.2 procedure [Hemming 2014] we calculated an overall sample size of 720 patients, which means 60 patients in each cluster for every detection period.

|            | t1  | t2  | t3  | t4  | t5  |
|------------|-----|-----|-----|-----|-----|
| c3= 5 unit | 60  | 60  | 60  |     | 60  |
| c2=5 unit  | 60  | 60  |     | 60  | 60  |
| c1 =5 unit | 60  |     | 60  | 60  | 60  |
|            | 180 | 120 | 120 | 120 | 180 |

## 8.7 Statistical analysis

Sample descriptive characteristics will be presented as means and standard deviation (SD) when normally distributed, or as medians and interquartile ranges (IQR). Although the majority of responses to individual items/symptom/functional scale of the EORTC QLQ-C30 questionnaire exhibits asymmetric distribution, findings will nevertheless be described with both mean and median values.

The main unit of analysis is the individual. Differences of HRQoL values between the two groups, post-intervention and control, relative to each of the two functional domains (emotional or social) of interest for the primary objective, will be analyzed using a binomial Beta regression model (BB), as suggested by different authors [Khan 2015, Arostegui 2012], due to the asymmetric distribution of values. This model also enables to estimate the strategy's effect in terms of Odds Ratio, the preferred measure by oncologists for its more immediate interpretation and greater usefulness in clinical practice, compared with HRQoL absolute values [Khan 2015]. To carry out the analysis with the BB model, responses will be transformed into a scale (0,1) by using the formula  $Y-a / b-a$ , where a and b are the lowest and highest possible scores, respectively, and Y is the observed response. For instance, a score of 80 will be expressed as  $80-0/(100-0) = 80/100 = 0.8$ .

Since the study is an incomplete, cross-sectional stepped-wedge cluster randomized controlled trial (with an implementation period) the following covariates will be included in the model: the implementation epoch (first, second or third) and time of exposure to the strategy; the cluster the patient belongs to (1, 2 or 3) and intra-cluster correlation [Hemming 2015, Stat Med].

The demographic and clinical variables which influence the outcome with a *p value* < 0.20 in the univariate analysis will be included in the regression model. Data analysis will be conducted using SAS v 8.1 and STATA/SE 11.2

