## 2. Objectives and ENDPOINTS

### 2.1 Primary objective

The primary objective is to assess the effectiveness of the HQIS vs standard care, in terms of improvement of at least one of the two functional domains of HRQoL, emotional or social, detected at baseline (before treatment initiation) and at clinical follow-up (approximately 3 months after study enrolment).

The primary endpoint will be measured using the EORTC QLQ-C30 questionnaire (see Paragraph 8.1), version 3.0 validated into Italian.

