### **7.2 Baseline assessment**

Prior to initiation of the first cycle of therapy, and before implementing the recommended interventions addressed to patients, a specially trained research nurse of the center will enter demographic and clinical variables (taken from medical records) into the electronic data collection form (eCRF), and will instruct the patients on how to complete the questionnaires using a tablet. The time needed for completion is estimated not to exceed 20 minutes for each patient (12 minutes for the EORTC and 8 minutes for the other questionnaires). The research nurse will check completeness of entered information, and in the case of missing data will invite the patient to fill in the empty fields, noting any problems arisen in the process.

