## **8.2 Variable coding**

The following main patient demographic and clinical characteristics are collected at baseline to describe the study population and determine factors associated with quality of life:

- Date of birth (dd/mm/yyyy)
- Gender (M/F)
- Civil status (married or living with partner, other)
- Education (primary, high-school and above)
- Date of diagnosis (dd/mm/yyyy)
- Presence of metastases (yes/no)
- Cancer site
- ECOG performance status
- Type of treatment (IV chemotherapy , oral drugs, molecular target drugs)

At three-month follow-up, presence of disease progression will also be recorded (yes/no). For questionnaires where information was missing (less than half of items was completed), reasons for non-completion will also be noted, i.e. patient withdrawal, patient refusal to complete the item, worsening of patient's health conditions hindering completion, patient lost to follow-up or deceased (see paragraph 8).

As for coding of QLQ-C30 questionnaire variables, responses are given on likert scales and the sum of assigned values yields the score for each of the 15 domains. Highest values in the symptom domain (e.g. Diarrhea, weakness, vomiting etc.) will indicate severe symptomatology. Highest values in the other domains will indicate better quality of life. Scores of each domain are linearly transformed into a 0-100 scale, where 0 and 100 are assigned to the lowest and highest possible value, respectively.

For the HADS-D scale [Annunziata 2011] a cut-off of >7 will be used, a score considered clinically significant (i.e. patients scoring above this value may benefit from psychological support therapy) and with high sensitivity (0.86) and specificity (0.81) [Vodermaier 2011]. Missing values will be replaced with

the mean of the available values for anxiety or depression, if not more than four values are absent. The NEQ detects the presence of different types of needs using dichotomic choices (yes/no). It will enable to assess the frequency of needs and to compare it across the two detection periods (baseline and follow-up). Specifically, this information will allow to determine whether the HQIS is effective in reducing needs and whether this also corresponds to a positive effect on quality of life.

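### The primary model omits the domain's baseline score, screens covariates at univariate p<0.20, and gives its beta-binomial response no denominator

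*Protocol*

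**What the plan says.** All of this is in the protocol.

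- **Objective (section 2.1).** Effectiveness is improvement in the emotional or social domain of the QLQ-C30, "detected at baseline (before treatment initiation) and at clinical follow-up (approximately 3 months after study enrolment").
- **Model (section 8.7).** Each domain "will be analyzed using a binomial Beta regression model (BB"), with the effect reported as an odds ratio.
- **Response (section 8.7).** The "responses will be transformed into a scale (0,1) by using the formula" (Y−a)/(b−a). The worked example takes a = 0 and b = 100 and turns a score of 80 into 0.8.
- **Fixed covariates (section 8.7).** The list is implementation epoch, exposure time and, to close it, "the cluster the patient belongs to (1, 2 or 3) and intra-cluster correlation".
- **Further covariates (section 8.7).** Demographic and clinical variables with a p value "< 0.20 in the univariate analysis will be included in the regression model".
- **Candidate pool (section 8.2).** "The following main patient demographic and clinical characteristics are collected at baseline": nine variables, none of them a QLQ-C30 score. The same section then adds disease progression, recorded at three months.
- **Analysis set (section 8.8).** The principal analysis takes only patients with both the baseline and the three-month assessment.

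**The concern.** Three rules in one section work against the primary comparison.

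**Baseline.** The objective is about improvement from baseline, but the modelled response is the raw score and the baseline score is not a stated covariate. Patients differ from epoch to epoch, there are only three geographical clusters, and the clinicians who screen patients are not blinded. Chance or selective differences in starting level between control and post-intervention patients would therefore stay in the estimate, and precision would be lost.

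**Screen.** Choosing covariates by their association with the outcome leaves the primary model unknown until the data are in. An odds ratio is non-collapsible, so its meaning changes with the covariates that pass. The two domains may end up with different models. Nothing limits the screen to baseline variables: progression (section 8.2) or ECOG at three months (section 7.3) could enter, and either may lie downstream of the intervention.

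**Response.** A beta-binomial likelihood is defined for a count out of a known maximum. The section supplies a fraction and no maximum.

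**Working it through.** **1. What the response is.** With a = 0 and b = 100, Y is a score on the 0–100 scale. A change score would run from −100 to 100. So the response is the raw score, and baseline could enter only as a covariate. It is neither in the fixed list of section 8.7 nor among the nine variables of section 8.2.

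**2. Value of the baseline score.** In a linear model, adjusting for a baseline that correlates r with follow-up multiplies the residual variance by 1 − r² and the standard error by √(1 − r²). The protocol gives no r, so a range is assumed:

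| r | 1 − r² | SE factor | SE reduction |
|---|---|---|---|
| 0.3 | 0.91 | 0.954 | 5% |
| 0.4 | 0.84 | 0.917 | 8% |
| 0.5 | 0.75 | 0.866 | 13% |
| 0.6 | 0.64 | 0.800 | 20% |

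A simulation of 576 completers (720 × 0.8), with 4,000 runs per scenario and a linear model with cluster and period effects standing in for the beta-binomial, agrees. The standard error of the effect, in SD units, fell from 0.241 to 0.222 at r = 0.4 and to 0.193 at r = 0.6. Power for a 0.3 SD effect rose from 0.23 to 0.27 and 0.34. These are linear-model figures and only a guide to the log-odds scale.

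**3. The screen.** Take nine independent candidates with no true effect, each passing with probability 0.20.

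- Expected number retained: 9 × 0.20 = 1.8 (simulated 1.76–1.82).
- Probability that at least one is retained: 1 − 0.8⁹ = 0.866.
- Simulated type I error with the screen: 0.044–0.053 against a nominal 0.05. The standard error stayed at 0.241.

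The screen therefore makes the model depend on the data, but no harm to the error rate was seen.

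**4. The response.** Take items 21–24 of the form in Attachment IV as the emotional scale and items 26–27 as the social scale, each scored 1–4. The protocol prints the items but does not assign them to scales, so this is an assumption.

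- Emotional: maximum count 4 × 3 = 12, so 13 levels in steps of 100/12.
- Social: maximum count 2 × 3 = 6, so 7 levels in steps of 100/6.
- A beta-binomial with 12 trials (illustrative shape parameters 2 and 1) has probability 0 at the value 0.8 and 11/91 = 0.121 at the count 10.
- For a complete scale, fraction × maximum returns the count: 83.33/100 × 12 = 10. The example's 80 gives 9.6 and 4.8, so it is not an attainable score. It serves only as an illustration, and nothing turns on it.
- If the model were fitted as a beta regression on the open interval, scores of 0 and 100 would become exactly 0 and 1, outside the support. In the case tested the log-density was minus infinity at both ends.
- Section 8.9 fills missing items with the mean of those answered when at least half are present. Applied within the emotional scale with one of four items missing, the count becomes the three-item sum × 4/3; a sum of 7 gives 9.33, which is not an integer.

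**5. Is baseline free of the intervention?** Section 7.2 places it "before implementing the recommended interventions addressed to patients". But section 7.1 puts screening after the first consultation with the oncologist, and section 5(a) makes staff training recommendation 1 of the strategy, with at least 75% of staff to complete it. In post-intervention epochs the baseline score therefore follows contact with a largely trained team and may already carry part of the effect.

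**The case against.** The best defence is that section 8.7 introduces its list as a consequence of the stepped-wedge design. It can be read as naming design terms without excluding others, and section 8 leaves statistical methods to an analysis plan not seen here. If the baseline score counts as a clinical variable, it would almost surely pass the screen: at r = 0.3 with 576 completers, t = 0.3 × √574 / √0.91 ≈ 7.5. The precision loss would then not occur. This limits the point but does not remove it. The section already states a covariate list, a selection rule and a transformation. On that text, the most useful covariate would enter only through a generous reading and a significance test.

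Three stronger readings are tempting and should not be drawn.

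- A reader might infer that the screen makes standard errors too small or inflates type I error. The simulation showed neither.
- A reader might infer that the named model cannot be fitted at all. The count can be recovered from the fraction once a maximum is stated, so the defect is the missing denominator.
- A reader might infer that patients with the best scores would be lost. That follows only under beta regression. Section 8.7 names a beta-binomial, for which the maximum count is valid data.

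It is also fair to object that conditioning on baseline has a cost if trained staff have already influenced it: the adjusted effect could be attenuated. That objection stands, and the fix allows for it.

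**Conclusion.** The point holds as a fault in three stated rules of section 8.7, and it should be corrected before the analysis plan is finalised.

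- **Baseline:** the same-domain score is not a stated covariate, although the objective rests on it and every analysed patient has it. Including it would lower the standard error by about 5–20%, assuming r of 0.3–0.6 and linear-model behaviour.
- **Screen:** the primary model and its conditional odds ratio depend on the data. At least one of nine independent noise candidates enters with probability 0.87. The two domains may get different models, and post-baseline variables are not excluded. The harm is to prespecification and interpretation; none to the error rate was shown.
- **Response:** no binomial denominator is given, and there is no rule for scores of 0 and 100 should the model be fitted as beta regression. This is easily repaired. The maxima of 12 and 6 rest on the item assignment assumed above.

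**What to change.** Amend section 8.7 and carry the change into the analysis plan.

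1. Enter the baseline score of the same domain as a fixed covariate in each domain's model, outside any selection step. Report a sensitivity analysis without it, because baseline in post-intervention epochs may carry part of the effect. Odds ratios with and without baseline can differ through non-collapsibility alone, so compare the two analyses on the mean-score scale as well.
2. Delete the p<0.20 screen. Replace it with one prespecified list of baseline variables already collected under section 8.2, identical for both domains. State that progression and ECOG at three months are not adjusted for. The choice of variables is the sponsor's; what matters is that it is fixed in advance.
3. Define the beta-binomial response at three months as a count out of a stated maximum: 0–12 for emotional (items 21–24) and 0–6 for social (items 26–27), with higher counts meaning better function. Give a rounding rule for scores that include mean-imputed items.

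The cost is wording in the protocol and analysis plan, plus one further analysis per domain. No new data are needed.

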## 8.8 Analyzed population

For the principal analysis of effectiveness, an Intention-to-treat population (ITT) is considered, composed of all eligible patients with HRQoL assessments at baseline and at 3-month follow-up. Patients are considered to be exposed to the intervention according to randomization, regardless of

any delay or failure to conduct the intervention. A “Per-protocol population” (PP) will also be assessed, composed of centers which will complete the trial without any breaches to the protocol and which exhibit a degree of compliance (% of trained clinicians and % of eligible patients who have received the intervention) greater than 75%. Sensitivity analyses will be conducted to assess the robustness of the missing data assumption made in the primary analysis.

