### a) Clinician training

The medical and nursing staff of participating centers will attend an Evidence-Based Medicine (EBM) course (recommendation 1) [Fallowfield 2003, Brown 2008, McLeod 2014] to improve communication-relational skills and to receive instructions on how to enact the recommendations of the project (Attachment II). Considering an average of 8 oncologists and 14 nurses for each center (based on the HuCare study experience), 2 editions of the course for oncologists and 3 editions for nurses will be provided for each cluster group, during a period of 6 consecutive weeks. All editions will be held on weekends in Milan, at the AIOM HuCare School for Communication in Oncology located at Palazzo delle Stelline. Each center must ensure that at least 75% of medical staff and nursing staff operating in the ward complete training.

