## **12.6 Changes to the protocol**

All amendments to the protocol shall be submitted to the ECs of participating centers. Amendments shall not be implemented before ethical approval is obtained. Changes merely concerning administrative or logistic aspects will be notified to the EC.

Should a violation to the protocol become necessary, the local study coordinator shall contact the principal investigator, possibly before the violation is implemented, or in any case as soon as possible, in order to discuss the matter and agree on the most appropriate course of action. Data reported in the CRF and in original documents will reflect all protocol violations and original documents will describe such violations and the circumstances that made them necessary.

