## ATTACHMENT I - FACILITIES QUESTIONNAIRE

Il presente progetto, promosso dall'Associazione Italiana Oncologia Medica, segue l'attuazione dello studio HuCare, finanziato nel 2009 dal Ministero della Salute e dalla Regione Lombardia e i cui risultati sono stati pubblicati di recente sulla rivista Supportive Care in Cancer. Lo studio ha dimostrato che è possibile trasferire interventi psicosociali "evidence-based" nella pratica clinica oncologica, attuando un'adeguata strategia di implementazione e garantendo il coinvolgimento di tutta l'equipe clinica (medici, infermieri, psicologi).

Il progetto HuCare2 ha l'obiettivo di valutare se l'applicazione di questa strategia, quindi di un set di interventi psicosociali, consente di migliorare la qualità di vita dei pazienti che iniziano un trattamento attivo. Il questionario è volto a verificare la presenza nel centro delle caratteristiche necessarie alla realizzazione degli interventi previsti dal progetto e a determinarne l'eleggibilità.

Vi preghiamo pertanto di rispondere alle seguenti domande, indicando, in caso di risposta negativa, le barriere all'introduzione dell'intervento, selezionando tra quelle indicate, tratte dalla letteratura, o specificando i motivi nel campo apposito se non presente nell'elenco.

---

Data presentazione del progetto a tutto il personale sanitario dell'U.O.      \_\_/\_\_/\_\_

1. Il Progetto prevede che tutto il personale medico svolga un corso residenziale di 3 gg per migliorare le proprie capacità comunicative. Tutte le edizioni dei corsi avranno luogo a Milano, presso la scuola di perfezionamento in comunicazione oncologica (Scuola AIOM-HuCare) situata nel Palazzo Stelline, nell'arco di due mesi (periodo assegnato al suo centro in base alla randomizzazione, vedi sinossi studio). I costi della formazione saranno coperti con i fondi del progetto, comprese le spese di trasferta, vitto e alloggio.

Lei conferma la possibilità che almeno il 75% dei medici oncologi (dipendenti e contrattisti a tempo determinato) del Suo reparto possano partecipare a tale corso?

☐ SI      ☐ NO      ☐ SOLO IN PARTE/PARZIALMENTE A CAUSA DI:

☐ carico di lavoro eccessivo, organizzazione del lavoro e indisponibilità di tempo

☐ disaccordo tra i membri dell'equipe

☐ mancanza di riconoscimento da parte della Direzione aziendale

☐ mancanza di consapevolezza dell'importanza

☐ mancanza di fiducia nell'efficacia dell'iniziativa

☐ altro \_\_\_\_\_

---

---

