2. Il Progetto prevede che tutto il personale infermieristico svolga un corso di formazione di 2 gg, per migliorare le capacità comunicative/relazionali e per gestire il PIS. Tutte le edizioni dei corsi avranno luogo a Milano, presso la scuola di perfezionamento in comunicazione oncologica (Scuola AIOM-HuCare) situata nel Palazzo Stelline, nel periodo assegnato al suo centro in base alla randomizzazione (vedi descrizione studio). I costi della formazione saranno a carico dei fondi del progetto, comprese le spese di trasferta, vitto e alloggio.

Lei conferma la possibilità che almeno il 75% degli infermieri del Suo reparto possano partecipare a tale corso?

☐ SI                      ☐ NO                      ☐ SOLO IN PARTE/PARZIALMENTE A CAUSA DI:

☐ carico di lavoro eccessivo, organizzazione del lavoro e indisponibilità di tempo

☐ disaccordo tra i membri dell'equipe

☐ mancanza di riconoscimento da parte della Direzione aziendale

☐ mancanza di consapevolezza dell'importanza

☐ mancanza di fiducia nell'efficacia dell'iniziativa

☐ altro \_\_\_\_\_

\_\_\_\_\_

\_\_\_\_\_

3. Il Progetto prevede l'introduzione di un percorso informativo e di accoglienza per tutti i nuovi pazienti prima dell'inizio della terapia. Tale percorso presuppone il coinvolgimento attivo del personale infermieristico e implica alcuni cambiamenti organizzativi.

Lei conferma la disponibilità del personale del Suo reparto ad introdurre questo nuovo percorso, illustrato nella breve descrizione delle attività del progetto allegata?

☐ SI                      ☐ NO                      ☐ SOLO IN PARTE/PARZIALMENTE A CAUSA DI:

☐ carico di lavoro eccessivo, organizzazione del lavoro e indisponibilità di tempo

☐ disaccordo tra i membri dell'equipe

☐ mancanza di riconoscimento da parte della Direzione aziendale

☐ mancanza di consapevolezza dell'importanza

☐ mancanza di fiducia nell'efficacia dell'iniziativa

☐ altro \_\_\_\_\_

\_\_\_\_\_

\_\_\_\_\_

4. Il Progetto prevede la disponibilità in ogni reparto di un luogo, anche di piccole dimensioni, da adibire all'allestimento del PIS (Punto di Informazione e Supporto) con le seguenti caratteristiche:

- Attiguo al DH e/o agli ambulatori del reparto di oncologia
- Possibilità di accesso a Internet
- Disponibilità di scaffale o armadio da allestire per biblioteca
- Garanzia di privacy per lo svolgimento del colloquio infermiere-paziente.

Lei conferma la disponibilità di allestire tale struttura nella sua U.O.?

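### The per-protocol population drops a whole centre for any protocol breach, and its compliance cut of more than 75% does not match the training requirement of at least 75%

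*Protocol*

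**What the plan says.** Section 8.8 names intention-to-treat as the principal population and adds a per-protocol population "composed of centers which will complete the trial without any breaches to the protocol". The same sentence adds a compliance condition on the share of trained clinicians and the share "of eligible patients who have received the intervention) greater than 75" per cent. It does not grade breaches as major or minor, and it does not say whether the trained share is taken within each profession or over all staff.

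The training duty in section 5, part a, is worded differently: "Each center must ensure that at least 75% of medical staff and nursing staff operating in the ward complete training". The facilities questionnaire (Attachment I) asks centres for the same minimum in two separate questions: "almeno il 75% dei medici oncologi" for medical oncologists and "almeno il 75% degli infermieri" for nurses. In both, the Italian means at least 75%.

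Section 12.6 deals with violations and states that "Data reported in the CRF and in original documents will reflect all protocol violations".

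**The concern.** A per-protocol analysis should show the effect where the strategy was actually delivered. The compliance condition serves that aim. The no-breach condition does not, because it also selects on errors of conduct that have nothing to do with delivery. Section 8.7 makes the individual the unit of analysis, yet an error in one patient's record, such as a wrong consent date, would remove every patient of that centre. A centre that enrols more patients has more chances to be excluded.

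The trial randomises only three clusters, one per implementation step. If all five centres of a cluster fail, a full sequence of the stepped wedge disappears from the analysis. The two training thresholds raise a smaller question: a centre could do exactly what section 5 asks and still fail the per-protocol cut.

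**Working it through.** **Inputs.** Section 8.6 gives an "overall sample size of 720 patients, which means 60 patients in each cluster for every detection period". Section 8.4 gives 15 centres in 3 clusters of 5. Section 5 gives the staffing: "Considering an average of 8 oncologists and 14 nurses for each center". The breach rate per patient, p, is not in the protocol. It is assumed here, over a range, with breaches independent between patients and enrolment equal between centres.

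**Patients per centre.** The layout reproduces the stated total: 3 clusters × 4 observed periods × 60 = 720, and by period 180 + 120 + 120 + 120 + 180 = 720. Per centre this is 720/15 = 48.

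**No-breach rule.** The probability that a centre has no breach is q = (1 − p)^48. The expected number of clean centres is 15q. The probability that at least one cluster loses all five centres is 1 − [1 − (1 − q)^5]^3. The probability that no centre is left is (1 − q)^15. These figures cover the no-breach condition alone, before the compliance cut is applied.

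| p | q | clean centres of 15 | a cluster fully lost | set empty |
|---|---|---|---|---|
| 0.5% | 0.786 | 11.8 | 0.1% | about 0 |
| 1% | 0.617 | 9.3 | 2.4% | about 0 |
| 2% | 0.379 | 5.7 | 25% | 0.1% |
| 5% | 0.085 | 1.3 | 95% | 26% |

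Expected patients kept under the centre rule are 720q: 444 at 1%, 273 at 2% and 61 at 5%. Removing only the patients with a breach would keep 720(1 − p): about 713, 706 and 684.

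**Threshold.** The smallest number of trained staff that satisfies each rule is:

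| Staff counted | at least 75% | more than 75% |
|---|---|---|
| 8 oncologists | 6 (75.0%) | 7 (87.5%) |
| 14 nurses | 11 (78.6%) | 11 (78.6%) |
| 22 pooled | 17 (77.3%) | 17 (77.3%) |

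The two rules part only when the staff count is a multiple of 4, because only then can a centre sit at exactly 75%. For the patient share, section 6 measures delivery on 5 consecutive cases per centre. That figure moves in steps of 20 points, and both rules require 4 of 5.

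**The case against.** Four points can be made for the plan.

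- **Section 12.6 does not predict violations.** A reader might infer from it that breaches are expected and the rule is bound to be triggered. The section is conditional: it says what to do should a violation become necessary, asks for prior contact with the principal investigator where possible, and gives no frequency. The stronger reading is not supported.
- **Some obvious examples of a breach are weak.** A late 3-month questionnaire breaks no stated limit, because the protocol only speaks of roughly three months. Ineligible enrolment is partly guarded against by the eligibility check built into the eCRF (section 8.3).
- **The threshold example depends on how staff are counted.** Section 6 defines the training outcome over oncologists and nurses together. An average-sized centre at the section 5 minimum has 6 + 11 = 17 of 22 trained, or 77.3%, and passes. The case of 6 of 8 oncologists fails only if medical staff are assessed separately. A per-protocol cut also need not equal the operational minimum.
- **The analysis is supporting, and grading of breaches is often left to the SAP.** The first half is correct. The second half helps less, because the protocol has already fixed a rule that covers every breach. An SAP that counted only major ones would depart from it.

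Independence is also pessimistic. If breaches concentrate in a few centres, more centres stay clean at the same average rate.

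**Conclusion.** The point holds as a defect in the wording of a supporting population. Applied literally, the rule removes 48 planned patients for one minor breach. Under the assumed independent breaches, it costs about 6 of 15 centres at 1% per patient, 9 at 2% and 14 at 5%. Loss of an entire cluster is the more serious prospect: unlikely at 1%, about one in four at 2% and close to certain at 5%.

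A reader might infer that the per-protocol set is likely to be empty. The documents do not support that: they give no breach rate, and the probability is about 0.1% at 2% and reaches 26% only at 5%. A reader might also infer that the cut above 75% will generally exclude centres that met the training requirement. It affects only a centre at exactly 75%, and at average staffing only if oncologists are assessed on their own.

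The intention-to-treat primary analysis and its conclusion are untouched.

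**What to change.** In section 8.8, delete the no-breach condition. Exclude instead individual patients with a major deviation, from a list fixed before unblinding. Candidates are ineligibility, enrolment in an earlier epoch, and a baseline questionnaire completed after the first cycle. A criterion on the timing of follow-up can be added only if a window is first defined. Before ineligibility is used, section 4.2 and the screening form in Attachment IV must be reconciled: they differ on the upper age limit and on the time since diagnosis.

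Keep compliance as a criterion for the whole centre, removing control and post-intervention data together. Dropping only the post-intervention data of a low-compliance centre would break the within-centre comparison, and the model in section 8.7 names cluster, not centre, so it would not adjust for that selection.

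Change the cut to 75% or more, and state whether it applies to each staff group, as the facilities questionnaire asks, or to pooled staff.

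The cost is wording in the protocol and SAP, with the protocol change handled as section 12.6 requires. The deviation list must be agreed in advance, and the per-protocol set becomes less strict.
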